## Abstract

**Introduction:**

Cardiovascular disease (CVD) is a major cause of mortality in renal transplant recipients (RTRs). General population risk scores for CVD underestimate the risk in patients with chronic kidney disease (CKD) suggesting additional non-traditional factors. Renal transplant recipients also exhibit elevated inflammation and impaired immune function. Exercise has a positive impact on these factors in patients with CKD but there is a lack of rigorous research in RTRs, particularly surrounding the feasibility and acceptability of high-intensity interval training (HIIT) versus moderate-intensity continuous training (MICT) in this population. This study aims to explore the feasibility of three different supervised aerobic exercise programmes in RTRs to guide the design of future large-scale efficacy studies.

**Methods and analysis:**

Renal transplant recipients will be randomised to HIIT A (16 min interval training with 4, 2 and 1 min intervals at 80%–90% of peak oxygen uptake (VO_2 peak_)), HIIT B (4×4 min interval training at 80%–90% VO_2peak_) or MICT (~40 min cycling at 50%–60% VO_2peak_) where they will undertake 24 supervised sessions (approximately thrice weekly over 8 weeks). Assessment visits will be at baseline, midtraining, immediate post-training and 3 months post-training. The study will evaluate the feasibility of recruitment, randomisation, retention, assessment procedures and the implementation of the interventions. A further qualitative sub-study QPACE-KD (Qualitative Participant Acceptability of Exercise in Kidney Disease) will explore patient experiences and perspectives through semistructured interviews and focus groups.

**Ethics and dissemination:**

All required ethical and regulatory approvals have been obtained. Findings will be disseminated through conference presentations, public platforms and academic publications.

**Trial registration number:**

Prospectively registered; ISRCTN17122775.

Strengths and limitations of this studyThis study provides a multidisciplinary approach with a variety of quantitative and qualitative outcome measures which will contribute to future large-scale randomised control trial design with focus on negative cardiovascular disease outcomes in renal transplant recipients (RTRs).This study addresses the urgent need to determine the feasibility of differing aerobic exercise types in RTRs to inform future advice and recommendations.This study specifically contributes to the limited literature on the feasibility of high-intensity interval training in solid organ transplant patients.As a limitation, the sample size is limited due to the study being centred on feasibility in preparation for future efficacy trials.

## Introduction

Cardiovascular disease (CVD) is a major cause of morbidity and mortality after kidney transplantation and a key factor limiting graft survival.^1 2^ Most recent data suggest that the proportion of mortalities in kidney transplant recipients attributed to CVD or stroke is 22%^3^; however, this figure does not emphasise the total impact on graft survival and quality of life of non-fatal events such as acute myocardial infarction, heart failure, stroke and cardiac arrhythmias.^2^ Numbers of transplants per year are currently rising,^3^ highlighting the need for cost-effective CVD prevention and risk factor management strategies for sustained patient health, graft survival and reduced healthcare burden.^4^

Traditional models of predicting CVD risk underestimate the risk in patients with chronic kidney disease (CKD) suggesting that kidney disease and transplantation introduce unique CVD risk factors not akin to the general population.^5^ Immunosuppressive medication can exacerbate traditional risk factors such as poor lipid profile, elevated blood pressure and the incidence of new onset diabetes.^6 7^ Weight gain, predominantly fat, is common in renal transplant recipients (RTRs) with 60% having a midarm fat area that is within the top 10% of values for the general population.^8^ Unique haemodynamic challenges (anaemia, hypertension and volume expansion) in RTRs can accelerate cardiomyopathy in the absence of the usual observation of concurrent ischaemic heart disease.^2^ These haemodynamic stresses are a likely contributor to the paradoxically common vascular and systemic inflammation observed in RTRs.^9^ Studies have suggested that elevations in novel biomarkers of inflammation are not just indicative but also contributory to CVD development.^10 11^

Empirical evidence suggests that physical activity has ‘anti-inflammatory’ consequences.^11^ Recent exercise intervention studies in kidney patients who have not reached end-stage renal disease demonstrate reduced traditional and novel markers of CVD risk and improved physical function.^12–14^ Similarly, dialysis patients have shown lowered markers of systemic inflammation^15^ and improvements in arterial stiffness.^16^ However, given its probable benefits, there is a shortfall in literature surrounding the role of physical activity in the management of CVD risk in RTRs.^17^ With a precarious balance of immune function and non-traditional CVD risk factors, current exercise guidelines may not be appropriate for this population.

Moderate-intensity continuous training (MICT) such as 30–40 min brisk walking on 3 days of the week^12^ or intradialytic cycling^15^ have been used and shown to be beneficial in reducing markers of CVD risk in patients with kidney disease. There has been a recent abundance of literature surrounding high-intensity aerobic protocols, particularly high-intensity interval training (HIIT) which suggests a greater improvement in traditional and inflammatory markers of CVD risk in clinical and non-clinical populations when compared with MICT.^18^ Although protocols differ, HIIT is characterised by short bursts of vigorous exercise (upwards of 80% maximal aerobic capacity) interspersed with periods of moderate intensity exercise or rest. In patients with CVD and heart transplant recipients, findings indicate that HIIT is well tolerated, safe and effective in improving CVD risk.^19–21^ Most recently, HIIT has been shown to be effective in improving physical function, inflammation and quality of life in peritoneal dialysis patients^22^; however, the effectiveness of HIIT versus MICT in RTRs has not yet, to our knowledge, been evaluated. With a lower time commitment and the aforementioned superior benefits, HIIT has the potential to provide a creditable alternative to MICT. This type of exercise has also been perceived to be more enjoyable than MICT,^23^ a key component for changing and maintaining physical activity levels in RTRs identified through qualitative methods.^24^ However, our patients’ views suggest that although HIIT may provide superior improvements of CVD risk factors with a shorter time commitment, the strenuous nature of the exercise might in itself present a barrier to participation in this population,^24^ and MICT such as brisk walking, may be more acceptable and encourage sustained participation.

Considering both the development of effective and sustainable exercise guidelines for lowering the CVD risk in RTRs and producing programmes with a wide appeal and good adherence, this pilot research aims to generate substantial foundations towards understanding the feasibility and acceptability of differing aerobic exercise protocols in this unique population. The finding will contribute to the growing body of information not only in this population but in other chronic disease populations at risk of CVD and also determine the feasibility of proceeding to large and complex randomised control trials with primary outcomes focusing on the reduction of negative CVD outcomes.

### Objectives

Primary objective

To evaluate the feasibility of a trial protocol involving three different supervised aerobic exercise programmes in renal transplant recipients.

Secondary objectivesTo assess participant experience and acceptability;To explore potential for impact on physical function, body composition, habitual physical activity and non-invasive CVD risk factors;To explore potential for impact on relevant blood, saliva and urinary markers of metabolic health, systemic inflammatory status and immune function;To assess the tolerability, practicality and patient perceived usefulness of these assessments of cardiovascular disease risk;To explore patient perception of their illness and symptoms, activity levels and quality of life.

## Methods and analysis

### PACE-KD trial design

The PACE-KD trial is a randomised, three-arm parallel-group study to determine the feasibility and acceptability of three different supervised aerobic exercise programmes. Figure 1 presents the study flow chart. There will be three parallel groups (exercise programmes): HIIT intervention A, HIIT intervention B and MICT (detailed below). Participants will be randomised to one of the three study arms and will complete 24 supervised sessions of the intervention (approximately three sessions per week over 8 weeks). After initial baseline testing, outcome measures will be attained at midtraining, immediate post-training and 3 months post-training. Additional acute outcome measures will be taken during one exercise session in the first 6 weeks and during one exercise session in the last 6 weeks of each exercise programme (see figure 2). Feasibility will be determined by assessing recruitment, compliance and completion. Acceptability and patient experience will be determined by a patient satisfaction questionnaire (PSQ) and an optional nested qualitative study (QPACE-KD) consisting of either one to one semistructured interviews or focus groups.

**Figure 1 F1:**
[figure not shown]
Study flowchart: overall study diagram. HIIT, high-intensity interval training; MICT, moderate-intensity continuous training; NICOM, Non-Invasive Cardiac Output Monitor; VO_2_, oxygen uptake.

**Figure 2 F2:**
[figure not shown]
Study flowchart: acute response sessions detailed diagram. NIRS, Near-Infrared Spectroscopy.

### Patient involvement

The study was designed in consultation with patient partners. A patient involvement (PPI) group has been convened (lead by JS) and will meet regularly with the rest of the research team to review progress and address any issues that arise. The PPI partners will particularly take part in the qualitative analysis and interpretation and dissemination of the results.

### Participants and recruitment

A total of 24 participants with an established kidney transplant will be randomised (via computerised random number generator) to either HIIT intervention A, HIIT intervention B or MICT (see table 1 for detailed inclusion and exclusion criteria). Patients will be screened by their own clinician for eligibility to enter the study. Eligible patients will be approached during their routine clinical appointments and will be provided with verbal and written study information. Additionally, eligible patients who have given prior consent to be contacted regarding research opportunities will be contacted via the post. All patients will be given the opportunity to discuss the study in more detail and the opportunity to consider their participation (at least 48 hours).

**Table 1 T1:** PACE-KD inclusion and exclusion criteria

Inclusion criteria	Exclusion criteria
Diagnosed with chronic kidney disease and are a renal transplant recipient Male or female, aged 18 years or over Received renal transplant >12 weeks prior to entering the study Is willing and able to give informed consent for participation in the study	Aged under 18 years Female participants who are pregnant, lactating or planning pregnancy during the course of the study Scheduled elective surgery or other procedures requiring general anaesthesia during the study Any other significant disease or disorder* Inability to give informed consent or comply with testing and training protocol for any reason

*That is, significant comorbidity including unstable hypertension, potentially lethal arrhythmia, myocardial infarction within 6 months, unstable angina, active liver disease, uncontrolled diabetes mellitus (HbA1c≥9%), advanced cerebral or peripheral vascular disease which, in the opinion of the patient’s own clinician, may either put the patient at risk because of participation in the study or may influence the result of the study or the patient’s ability to participate in the study.

### Interventions

Each exercise programme will consist of 24 sessions over approximately 8 weeks. Participants will be allowed to drink plain water during exercise sessions. The programmes will be based on the three protocols described below.

#### HIIT programme A: (figure 3A)

Each session will consist of 16 min interval training with intervals of 4, 2 and 1 min duration at 80%, progressing to 90% oxygen uptake peak (VO_2 peak_) over the 8 weeks, separated by a 2 min active rest (~60% VO_2 peak_) giving a total exercise time of 30 min.

**Figure 3 F3:**
[figure not shown]
Schematic diagram of HIIT regimens A and B. Each block shows stage duration in minutes. The final 5 min stage has been added to HIIT programme B to ensure the overall work done is matched for both protocols. HIIT, high-intensity interval training, VO_2_, oxygen uptake.

#### HIIT programme B: (figure 3B)

Each supervised session will consist of 4×4 min of interval training at 80% VO_2 peak_, progressing to 90% VO_2 peak_ over the 8 weeks, separated by a 3 min active rest (~60% VO_2 peak_) and with a final 5 min recovery stage to ensure that overall work done is matched for both HIIT protocols, therefore also giving a total exercise time of 30 min.

#### MICT exercise intervention

Each supervised session will consist of continuous brisk cycling for ~40 min with a target rating of perceived exertion (RPE)of 12–14 (somewhat hard). This is equivalent to 50%–60% VO_2 peak_ and will be matched to the HIIT protocols for total external work done based on calculations of percentage of peak watts obtained from the VO_2 peak_ test. In this way, for each individual the overall energy expenditure during the session would be the same regardless of the trial they are assigned to.

All exercise sessions will be preceded by a 5 min low intensity warm up and followed by a 10 min cool down.

### Study procedures

The study outcomes, measurement methods and assessment time periods are summarised in table 2, and a detailed overview of each measurement is provided at the end of this section. Data on recruitment, numbers of sessions attended and completed in accordance with the protocol and dropout will be recorded and continuously monitored.

**Table 2 T2:** PACE-KD outcomes, measurement methods and assessment time periods

Outcome	Measurement method/tool	Time period
Feasibility	Recruitment, compliance, dropout and completion percentages	Continuous
VO_2 peak_	CPET	Baseline, post-training
Physical function	Gait speed test	Baseline, midtraining, post-training, three months post-training
	Sit to stand test	
	Plantar flexion strength (Fysiometer)	
Body composition	BIA	Baseline, midtraining, post-training, three months post-training
Heart function	NICOM	Baseline, midtraining, post-training, three months post-training
Arterial stiffness	PWV (applanation tonometry)	Baseline, midtraining, post-training, three months post-training
SpO_2_	Pulse oximetry	Baseline, midtraining, post-training, three months post-training, acute response sessions
Habitual physical activity	Accelerometry	Baseline, post-training
Muscle O_2_saturation	NIRS	Acute response session
Urinary bacteriuria	Urine sample	Baseline, midtraining, post-training
Immune function	Blood and saliva samples	Baseline, midtraining, post-training, three months post-training, acute response sessions
Markers of inflammation, oxidative stress, CVD risk	Blood samples	Baseline, midtraining, post-training, three months post-training, acute response sessions
Renal profile	Blood samples	Baseline, post-training
Clinical information	Extraction from clinical notes	Baseline, midtraining, post-training, three months post-training
Renal symptoms	POS-S	Baseline, midtraining, post-training, three months post-training
Fatigue	Fatigue scale	Baseline, midtraining, post-training, three months post-training
Quality of life	EQ-5D	Baseline, midtraining, post-training, three months post-training
Illness perception	IPQ-R	Baseline, midtraining, post-training, three months post-training
Physical activity/functional capacity	DASI	Baseline, midtraining, post-training, three months post-training
Pain	BPI	Baseline, midtraining, post-training, three months post-training
Sleep quality	PSQI	Baseline, midtraining, post-training, three months post-training
Daytime sleepiness	ESS	Baseline, midtraining, post-training, three months post-training
Illness symptoms	PACE-KD Illness-Symptom Questionnaire	Before each exercise session and ×1 at the weekend between sessions
Tolerability, practicality, acceptability and perceived usefulness of the study measures	PSQ; Semi-structured interview or focus group	Post-study involvement; Post-study involvement through optional QPACE-KD nested qualitative study

BIA, Bioelectrical Impedance Analysis; BPI, Brief Pain Inventory; CPET, Cardiopulmonary Exercise Test; CVD, Cardiovascular Disease; DASI, Duke Activity Status Index; EQ-5D, EuroQol 5 Dimension; ESS, Epworth Sleepiness Scale; IPQ-R, Illness Perception Questionnaire—Revised; NICOM, Non-Invasive Cardiac Output Monitor; NIRS, Near-Infrared Spectroscopy; POS-S, Renal Patient Outcome Scale; PSQ, Patient Satisfaction Questionnaire; PSQI, Pittsburgh Sleep Quality Index; SpO2, Peripheral Oxygen Saturation; VO_2peak_, peak oxygen uptake.

#### Baseline visit (visit 1)

At visit 1, informed consent will be obtained on arrival. Participants will perform a standard maximal exercise test (VO_2 peak_ test) in the presence of a cardiac nurse. This test will be preceded by a 12-lead ECG and subject to the confirmed absence of any contraindications.

Measurements of cardiac function, physical function, anthropometry, body composition and blood, urine and saliva samples will be collected. A survey pack will be completed and an accelerometer given to measure habitual physical activity over approximately 7 days.

#### Training visits

Participants will attend 24 supervised exercise sessions (approximately three per week for 8 weeks) of either: HIIT A, HIIT B or MICT (as outlined above). At the beginning of each session, participants will be asked to complete an internally designed illness–symptom questionnaire. They will also be provided with a copy to complete over the weekend between sessions. The questionnaire will provide data on illness symptoms particularly relating to upper respiratory, digestive and urinary tract.

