### Sample size

As the trial has a primary outcome of feasibility the study sample size is pragmatic and a power calculation is neither relevant nor possible. Data collected on secondary outcome measures will provide data on which sample size calculations can be performed in future well-informed randomised controlled trials. We have chosen specific and relevant secondary outcome variables that may be suitable future primary outcomes.

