### Data analysis

The primary outcome will assess the feasibility of study components such as recruitment, randomisation, retention, assessment procedures and the implementation of the interventions. These will be quantified by analysing factors such as but not limited to: numbers screened, numbers enrolled, proportion of eligible patients enrolled, intervention-specific retention rates, rates of adherence to protocol per intervention and proportion of training sessions and assessment sessions completed. The criteria for determining study and intervention feasibility will be as follows: Compliance: attending >70% of sessions and retention/completion:>80% of participants.

Due to the small sample size, complex statistical analysis will not be performed on the secondary outcomes; however, we will use simple analysis (eg, t-test, linear regression) to investigate statistical differences for exploratory information only.

Interview data will be analysed according to the principles of interpretive thematic analysis using a framework approach^42^ to explore themes emerging from patient journeys through and experiences of the interventions and outcome measures. The whole research team, including patient partners, will be involved in qualitative analysis to avoid individual bias.

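### About three in four planned illness-symptom forms depend on attending a session, so a short weekday illness that keeps a participant away can go unrecorded

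*Protocol article*

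**What the plan says.** The Training visits section of the protocol article plans 24 supervised sessions at roughly three a week for 8 weeks. It states that "At the beginning of each session, participants will be asked to complete an internally designed" illness-symptom questionnaire, and then: "They will also be provided with a copy to complete over the weekend between sessions". Table 2, under Study procedures, gives the same timing: "Before each exercise session and ×1 at the weekend between sessions".

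On content, the article says: "The questionnaire will provide data on illness symptoms particularly relating to upper respiratory, digestive and urinary tract". It gives no recall period.

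On attendance, Study procedures says: "Data on recruitment, numbers of sessions attended and completed in accordance with the protocol and dropout will be recorded and continuously monitored". The Data analysis section sets the feasibility criteria as "Compliance: attending >70% of sessions and retention/completion:>80% of participants" and describes the analysis of secondary outcomes as simple and exploratory.

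**The concern.** The rule for collecting the form is linked to the thing the form measures. A respiratory, digestive or urinary illness is a plausible reason for an immunosuppressed participant to stay away from a supervised session. When that happens, the schedule yields no session form for that day. The forms that do exist then come disproportionately from days on which the participant was well enough to attend, and they hold no information with which to correct for this.

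Two things are at stake. The first is the level of recorded illness, which may be too low. The second is the exploratory comparison between the two HIIT arms and MICT, which could be distorted if participants in one arm are more inclined than those in another to stay away when ill. The Sample size section intends the secondary outcomes to inform the design of later trials, so it is useful to know that this instrument captures what it is meant to capture.

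**Working it through.** The article states no figure for this point, so there is none to reproduce. The check has three parts.

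**1. How many planned forms depend on attendance.** Inputs: 24 sessions (Training visits) and one form per weekend (Table 2). Eight weeks contain 7 weekends between sessions, or 8 if the last is counted.

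- Planned forms: 24 + 7 = 31, or 24 + 8 = 32.
- Tied to a session: 24/31 = 77%, or 24/32 = 75%.
- Not tied to a session: 7/31 = 23%, or 8/32 = 25%.

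**2. What the compliance criterion allows.** This reads the criterion of more than 70% of sessions as applying to each participant. The smallest whole number above 70% of 24 is 17, since 17/24 = 70.8%.

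- Session forms that can be absent in a compliant participant: 24 − 17 = 7, and 7/24 = 29%.
- Forms still possible if every weekend form is returned: (17 + 7)/31 = 77%, or (17 + 8)/32 = 78%.

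This is what the criterion tolerates. It does not forecast attendance, and nothing in the article ties those absences to illness.

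**3. What the weekend form recovers.** The assumptions here are not in the article: sessions on Monday, Wednesday and Friday; one weekend form on Sunday; every session during the illness missed; a form that asks only about current symptoms; and illness equally likely to start on any day of the week. For each duration, count over the 7 possible start days how many illnesses overlap a session, and how many of those do not overlap a Sunday.

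| Duration (days) | Start days overlapping a session | Of these, no Sunday overlap | Share on no weekend form |
|---|---|---|---|
| 1 | 3 of 7 | 3 | 3/3 = 100% |
| 2 | 6 of 7 | 5 | 5/6 = 83% |
| 3 | 7 of 7 | 4 | 4/7 = 57% |
| 4 | 7 of 7 | 3 | 3/7 = 43% |
| 5 | 7 of 7 | 2 | 2/7 = 29% |
| 7 or more | 7 of 7 | 0 | 0% |

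The weekend form therefore covers an illness of a week or more, if it is returned, and covers short weekday illness only in part. A form that asked about all days since the last one would lower these shares, because the next session or weekend form would pick up the missed days.

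**The case against.** The strongest objection is that the schedule already reaches beyond attended sessions. A reader might infer that a participant who stays away ill supplies no form at all. The documents do not support that: the weekend copy appears both in Training visits and in Table 2, and long illnesses, arguably the more important ones, would overlap it. A reader might also infer that someone absent for a whole week has no weekend copy. The article does not say when or how copies are handed out, and a supply given at the start would fit its wording.

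Second, the questionnaire is not reproduced. If it already looks back to the previous form, little is lost. Operational details such as this are often left to the full protocol, so their absence from an article is not itself a fault.

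Third, it is tempting to conclude that the HIIT versus MICT comparison is biased. That would need illness-related absence to differ by arm. The Introduction raises the strenuous nature of HIIT as a possible barrier to participation, but that is not evidence of differential absence through illness. The outcome is exploratory in 24 participants, and Table 2 has other health information, such as extraction from clinical notes, renal symptoms and bacteriuria, that does not depend on attending a particular training session.

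All of this limits the point. What it leaves standing is the stated timing: the weekday forms are attached to sessions, and neither the text nor Table 2 schedules a form for a weekday session that is missed. Making up a missed session within the approximate 8 weeks would restore the number of forms, but would not by itself record the ill day.

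**Conclusion.** The point holds in a limited form. The stated schedule makes 75% to 77% of planned illness-symptom forms conditional on attendance, and that attendance can plausibly depend on the illness being recorded. Illness may therefore be under-recorded, mainly short weekday episodes. The shares in the table show how far the weekend form helps, but they rest on an assumed weekly timetable, complete absence during illness and no look-back.

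The overall size of any under-recording cannot be fixed, because the article gives no illness rate, no rate of illness-related absence and no recall period. Distortion between arms is possible only if illness-related absence differs by arm, and its direction is likewise unknown. The compliance and retention criteria do not use this questionnaire and are unaffected. This is a worthwhile improvement to an exploratory measure, and it leaves the primary feasibility objective untouched.

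**What to change.** Attach the form to the scheduled session whether or not it is attended:

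- For every scheduled session that is missed, have the same form completed remotely, on a take-home copy or in a short phone call, and record the reason for absence. Do this for the original date even if the session is later made up.
- Word the form to cover the period since the last form was completed, and state that recall period.
- Summarise illness over scheduled days rather than attended days, and report by arm how many forms were completed in person, completed remotely or missing.

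The cost is a short call for each missed session and a few more paper forms. No new instrument, visit or staff is needed.
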